### Intervention description

The standard intervention is based on the physiotherapy clinical practice guidelines, updated by the JOSPT for knee injuries, which include lower limb massage, mobilization, neuromuscular strengthening and rehabilitation, teachings, quadriceps neuromuscular electrical stimulation and cryotherapy [3]. The intervention group will complete the four-week rehabilitation program, with five sessions per week, performed and supervised by the physiotherapist. All patients follow the same order of treatment and exercises, starting with massage and mobilization, followed by the corresponding exercise program, and ending with Neuromuscular Electrical Stimulation (NMES) and cryotherapy (Table 1). This four-week intervention for rehabilitation of the knee joint after surgery makes it possible to improve passive and active knee extension (knee extension range of motion), increase quadriceps strength, improve gait performance, and optimize the patient's functionality. The control group will follow a standard six-week rehabilitation program.

### Evaluation

We have three evaluations of each group: a baseline assessment, before the intervention, a 2nd evaluation right after the end of the intervention, and a 3rd, six months after the intervention.

## Discussion

This experimental clinical study makes it possible to assess the quality of life reported by participants with knee pathology who take part in a rehabilitation program after surgery. In rehabilitation after surgery, measuring results is fundamental, and focuses on assessing function, activity, and participation [7]. There is nowadays a tendency to obtain the patient's perspective through PROMs, as they include scores related to satisfaction and health-related quality of life [8]. Satisfaction and health-related quality of life are key elements in understanding the effectiveness of rehabilitation programs, making it possible to mitigate the consequences associated with knee pathology, improve the rehabilitation process, and adapt health care to the population [8].

The significant importance that patient satisfaction and quality of life has assumed in health care is in line with the construction and development of this project, promoting positive changes in health status and in the services provided through a rehabilitation program [9]. The evaluation is based on the recording of data throughout the program, focusing on the self-perception of the participants in the group with the four-week structured program and in the group with the six-week regular program.

We intend to contribute with recommendations regarding the application of PROMs used in rehabilitation programs after knee pathology, in relation to motivation, satisfaction and health-related quality of life.

## Statistical methods

The Statistical Package for Social Sciences (SPSS®) 29 software (IBM Corp, Armonk, New York, USA) will be used. Different statistical procedures will be used to analyze the data, including descriptive and inferential techniques. Non-parametric tests, Chi-square and Mann-Whitney U will be used when the normality of the distribution is not verified. If normality or small deviations allow the use of parametric tests, we will apply the Student's *t*-test for independent measures.

The differences between the groups at the different assessment times will be calculated using a two-factor ANOVA. A Multiple Linear Regression will be carried out with each dependent variable and the intervention to analyze its effect on the different outcomes found. For the statistical tests, a 95 % confidence level will be considered, even if the p-values do not indicate a significant difference, we will report the effect size to give meaning and emphasize the power of the results [10].

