### Procedures

Participants will complete the intervention described in Table 1, based on the updated Journal of Orthopaedic and Sports Physical Therapy (JOSPT) guidelines for knee injuries [3].

**Table 1 tbl0001:** Knee treatment intervention protocol.

Interventions	week			
	1	2	3	4
Massage	x	x	x	x
Passive Mobilization	x	x		
Active Mobilization	x	x	x	x
Neuromuscular Electrical Stimulation (NMES)	x	x	x	x
Proprioceptive Training		x	x	x
Isometric Exercises: Quadriceps; Vastus Medialis Oblique Muscle (VMO); Hip Adduction	x	x		
Isotonic Exercises: Gastrocnemius	x	x		
Isotonic Exercises: Quadriceps; Hip extension; Hip adduction; Hip abduction; Hamstrings	x	x	x	x
Standing Isotonic Gastrocnemius Exercises		x	x	x
Wall Slide 0° to 30°		x		
Wall Slide 0° to 45°			x	
Wall Slide 0° to 90°				x
Static Ergometer		x	x	x
Treadmill Progression: gait>run				x
Single Leg Vertical Jump				x
Specific Sport Exercises				x
Lower Limbs Stretching	x	x	x	x
Cryotherapy	x	x		

Initial data will be collected at baseline (T0), the intervention will then take place, an evaluation will be carried out shortly after the end of the intervention (T1) and the final evaluation will be carried out 6 months after the end of the intervention (T2). The following PROMs will be applied before and after the intervention:-The “**EQ-5D-5L**” instrument comprises five dimensions, each describing a different aspect of health: Mobility, Self-care, Usual activities, Pain/discomfort, and Anxiety/depression. Each dimension has five response levels: no problems, slight problems, moderate problems, severe problems, unable to/extreme problems. The visual analogue scale of this questionnaire has a score of 0–100. Higher scores mean better quality of life and lower scores indicate lower quality of life [4];-The “**HADS**” instrument, developed to detect symptoms of anxiety and depression, is made of 14 items, subdivided into two subscales - Anxiety and Depression, with a maximum score of 21 points for each subscale. The subscale scores can be calculated separately or together, with each item scored from 0 (absent) to 3 (extremely present) [5];-The “**BREQ2**” instrument has 19 items with five response options on a Likert scale, where 0 is "not true for me" and 4 is "often true for me" to assess the constructs of: amotivation, external regulation, introjected, identified and intrinsic motivation. The results can vary from 24 (lowest self-determination) to 20 (highest self-determination) [6].

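### An undefined normality check decides which two-group test is run, and chi-square is listed as a fallback for non-normal scores although it ignores their order

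*Protocol article*

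**What the plan says.** The Statistical methods section of the protocol article gives a conditional rule for comparing the two groups. One branch reads "Non-parametric tests, Chi-square and Mann-Whitney U will be used when the normality of the distribution is not verified". The other opens "If normality or small deviations allow the use of parametric tests" and leads to Student's t-test for independent measures. The section names no normality test, sets no limit on how small a deviation must be, and does not say which fallback belongs to which variable.

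Two further analyses follow without any normality condition: "The differences between the groups at the different assessment times will be calculated using a two-factor ANOVA", and "A Multiple Linear Regression will be carried out with each dependent variable and the intervention to analyze its effect".

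The outcomes described under Procedures are ordered or bounded scores. For the EQ-5D-5L, "Each dimension has five response levels: no problems, slight problems, moderate problems, severe problems, unable to/extreme problems". For its scale, "The visual analogue scale of this questionnaire has a score of 0–100". Each HADS subscale has a maximum of 21, and BREQ2 is built from Likert items. All are collected at T0, T1 and T2.

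**The concern.** Three things are badly fixed in the two-group rule.

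- **What is compared.** A t-test compares means and Mann-Whitney compares ranks. Which one is reported for an outcome is settled only after the data are seen, by a criterion that leaves room for judgement. Results for different outcomes could end up on different scales.
- **Chi-square as a fallback.** Chi-square is a test for unordered categories. As the sentence stands, it is offered as an answer to non-normality. Used on ordered levels it discards their order, and with small groups its cell counts are thin.
- **Internal fit.** A score judged too non-normal for a t-test would still go into an ANOVA and a linear regression, both normal-theory models, with no alternative route for either.

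At stake are a clearly defined treatment comparison and, if chi-square were used on ordered items, a large part of a power that the plan already sets at only 0.5.

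**Working it through.** **Inputs.** From Sample size calculation: alpha 0.05, power 0.5, effect size 0.5, minimum 60 patients, 20% loss, 75 recruited. Assumed, because the article does not state them: effect size is a standardised mean difference, tests are two-sided, allocation is 1:1 (60/2 = 30 per group analysed), and all score distributions below.

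**1. The plan's own figure.** n per group = 2(z₀.₉₇₅ + z₀.₅)²/d² = 2 × (1.960 + 0)²/0.5² = 30.7, so 31 per group and 62 in total. This is close to the stated 60. With loss, 60/(1 − 0.20) = 75, as stated. At 30 per group, power for a t-test is Φ(0.5 × √15 − 1.960) = Φ(−0.024) = 0.49 by the normal approximation and 0.478 exactly.

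**2. Simulation of the rule.** 30 per group, 3,000 trials per scenario, two-sided 0.05. The check was represented by Shapiro-Wilk at 0.05 in either group, itself an assumption.

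Power at a 0.5 SD shift:

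| Assumed score | t-test | Mann-Whitney | Chi-square | t and Mann-Whitney disagree |
|---|---|---|---|---|
| Five levels (normal latent variable cut at −0.6, 0.2, 0.9, 1.7) | 0.444 | 0.434 | 0.246 | 3.6% |
| Skewed 0–21 score (gamma, shape 2, scale 3) | 0.511 | 0.612 | 0.149 | 13.7% |
| Near-normal score (mean 60, SD 15) | 0.477 | 0.449 | 0.001 | 8.2% |

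Under no effect:

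| Assumed score | Rejections, gated rule | Rejections, smaller p of t and Mann-Whitney | Check flags non-normality |
|---|---|---|---|
| Five levels | 0.052 | 0.059 | 100% |
| Skewed 0–21 | 0.047 | 0.061 | 95.6% |
| Near-normal | 0.053 | 0.061 | 10.5% |

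The simulation error of a 0.05 rate is √(0.05 × 0.95/3000) = 0.004. A separate run gave 5.7% for the gated rule, 5.5% for the t-test alone and 6.2% for the smaller p. The gate is therefore close to nominal. Its effect is on which quantity is reported: with a true shift, the two tests reach different conclusions in about 4% to 14% of trials.

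**3. Chi-square on five-level items, other assumptions.** With level probabilities 0.25/0.30/0.25/0.15/0.05 and a logistic shift of 0.5 SD (4,000 trials), power was 0.281 for chi-square and 0.493 for Mann-Whitney. With a normal shift it was 25% and 44%. Over all runs the ranges were 23–28% and 43–49%. Expected counts are low: with no shift, the top two levels give 30 × 0.05 = 1.5 and 30 × 0.15 = 4.5 per group, both below 5. At least one expected count fell below 5 in 99% of simulated trials.

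**4. What one fixed, baseline-adjusted model gives.** With correlation r between T0 and follow-up, the residual SD shrinks by √(1 − r²), so power ≈ Φ(0.5√15/√(1 − r²) − 1.960).

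- r = 0.3: Φ(2.030 − 1.960) = 0.53
- r = 0.5: Φ(2.236 − 1.960) = 0.61 (about 59% in simulation, against 49% for t and 45% for Mann-Whitney)
- r = 0.7: Φ(2.712 − 1.960) = 0.77

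The article gives no value for r.

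**The case against.** The strongest reply is that the between-group comparison over time is assigned, unconditionally, to the two-factor ANOVA, and the effect on each outcome to regression. The t, Mann-Whitney and chi-square tests may be meant only for baseline or descriptive comparisons. This stands in part. A reader might infer that the whole treatment comparison shifts with the data, and the article does not support that. But it does not confine the gated tests to baseline either, nor say which analysis answers the main aim.

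Second, chi-square may simply have been meant for categorical variables, with Mann-Whitney for scores. That is plausible, and the article nowhere says that EQ-5D-5L dimensions will be tested singly by chi-square. The power loss is therefore conditional on that use. The sentence still ties chi-square to failed normality and not to variable type, so it needs correcting on either reading.

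Third, a reader might infer that choosing the test from the data seriously inflates false positives. It does not: the gate gives about 5–6%. Rates of 9–10% can be produced by taking the smaller p-value of an unadjusted and a change-score analysis, but that reflects baseline handling, and the article names no change-score analysis. Such figures should not be used here.

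Finally, details of test selection are often left to an analysis plan that is not shown. The point here is not an omission: the article states a rule, and the rule as stated is poorly fixed.

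**Conclusion.** The point holds for the two-group tests only. For those, the quantity compared is not fixed in advance, the criterion for switching is undefined, and the logic conflicts with two ungated normal-theory analyses of the same outcomes. Chi-square is wrongly described as a fallback for non-normality. If it were used on five-level items, power would drop from roughly 43–49% to 23–28%. That range rests on 30 per group, 1:1 allocation, a 0.5 SD shift and assumed level distributions and latent shapes. How often the switch would operate also depends on assumed distributions. Type I error is not a material problem. This is worth correcting before analysis, but it does not undermine the trial.

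**What to change.** Replace the conditional rule with one stated method per outcome type:

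- **VAS, HADS and BREQ2 scores:** a linear model of the follow-up score on group and the T0 score, reported with a robust or bootstrap 95% confidence interval (name one), whatever the distribution. The regression already planned can carry this once T0 is named as a covariate.
- **EQ-5D-5L dimensions, if tested singly:** ordinal logistic regression on group and T0 level, as the only method.
- **Nominal variables:** chi-square, or Fisher's exact test when cells are small, and nowhere else.

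The cost is wording and slightly more analysis work, with no new data because T0 is already collected. There is one trade-off. On a strongly skewed score a comparison of means can be less powerful than ranks (0.511 against 0.612 in the unadjusted example above). Baseline adjustment offsets this to a degree that depends on the T0 correlation. The ordinal model assumes proportional odds, and sparse levels may need a merging rule set beforehand.

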### Sample size calculation

GPower@ software was used to calculate the sample size, determining a minimum of 60 patients assuming an alpha error of 0.05, a sample power of 0,5 (Power = 1-β err prob), and an effect size of 0,5. Anticipating a potential loss of 20% in follow-up due to the period required for the program (with evaluation at 6 months) and based on the numbers from each of the centers, a total of 75 patients will be recruited.

The experimental group will complete the rehabilitation program, in which the intervention takes place in five sessions per week over 4 weeks, with the physiotherapist supervising all the sessions (Fig. 1).

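### Overlapping tests of the group effect, each at 5% and none decisive, put the false-positive risk for a single score at roughly 7% to 13%

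*Protocol article*

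**What the plan says.** The Statistical methods section of the protocol article lists three kinds of inferential analysis.

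- **Two-sample test.** Where normality allows, "we will apply the Student's *t*-test for independent measures"; otherwise Mann-Whitney U takes its place. The text does not say which variable or visit this test serves.
- **Two-factor ANOVA.** "The differences between the groups at the different assessment times will be calculated using a two-factor ANOVA". The text does not say whether the group term or the group-by-time term is to be read.
- **Regression.** "A Multiple Linear Regression will be carried out with each dependent variable and the intervention to analyze its effect on the different outcomes found". No covariates are named, so adjustment for the baseline score is left open.

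One sentence sets the level for all of them: "For the statistical tests, a 95 % confidence level will be considered". Nothing ranks the analyses or calls any of them supportive. The Sample size calculation section gives a single error rate and a single effect size: "determining a minimum of 60 patients assuming an alpha error of 0.05", "a sample power of 0,5", "and an effect size of 0,5".

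**The concern.** The ANOVA and the regression are both explicitly directed at the difference between groups on the same outcomes, and the two-sample test may be as well. They do not estimate the same quantity. A two-sample test or regression at one visit compares levels at that visit. The ANOVA group term compares averages over all three visits, baseline included. The interaction compares change over time. Each is correlated with the others but can cross 5% by itself.

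Two consequences follow. If the programme has no effect, there is more than one opportunity per score to find p<0.05, so the error rate for a claim exceeds the stated 5%. If the programme does have an effect, one analysis may be significant and another not, and the article gives no rule for deciding which answers the quality-of-life objective. Fixing one score and one visit, or giving the ANOVA a proper within-patient factor, would not remove this.

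**Working it through.** **Inputs from the article.** Alpha 0.05, power 0.5, effect size 0.5, minimum 60 patients, 20% loss, 75 recruited (Sample size calculation); two groups; three evaluations, T0, T1 and T2 (Procedures; Evaluation).

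**Assumptions, because the article does not state them.** 1:1 allocation (30 evaluable per arm), two-sided tests, effect size read as a standardised mean difference, normal scores, equal correlation between visits, no missing data. Correlation is varied from 0.2 to 0.8.

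**Step 1: reproduce the planned size.** n per arm = 2(1.960 + 0)²/0.5² = 30.7, so 31 per arm and 62 in total, within two patients of the stated 60. Power at 30 per arm = Φ(0.5·√(30/2) − 1.960) = Φ(1.936 − 1.960) = 0.491. Recruitment: 60/(1 − 0.20) = 75. So 30 per arm is a fair basis for what follows.

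**Step 2: tests simulated for one score.**
- t-test at T1: difference in means divided by s√(2/30), 58 df.
- ANOVA group term: the same test on each patient's mean over the three visits.
- ANOVA group-by-time term: F with 2 and 116 df.
- Regression at T1 on group and baseline score: test of the group coefficient, 57 df. Without the baseline score this is the t-test itself.

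Each test alone rejects in about 5% of null trials (4.8% to 5.2%).

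**Step 3: chance of at least one p<0.05 when there is no effect** (correlation 0.2 to 0.8 unless noted)

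| Analyses that may support a claim | Risk |
|---|---|
| t-test (or unadjusted regression) + ANOVA group term | 6.9% to 8.5% |
| t-test (or unadjusted regression) + interaction | 8.7% to 9.7% |
| Interaction + adjusted regression, no t-test (correlation 0.3 to 0.7) | about 8% |
| t-test + group term + adjusted regression | 9.4% to 10.7% |
| t-test + interaction + adjusted regression | 9.2% to 11.7% |
| Both ANOVA terms + adjusted regression, no t-test (correlation 0.3 to 0.7) | about 12% |
| t-test + both ANOVA terms + adjusted regression | 12.6% to 13.3% |

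For reference, three independent tests would give 1 − 0.95³ = 14.3%.

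**Step 4: how often two analyses differ**, meaning one has p<0.05 and the other does not. The true effect is 0.5 SD at T1 and T2, with 30 per arm and correlations of 0.3, 0.5 and 0.7.
- Adjusted regression against interaction: 34%, 29%, 21%.
- t-test against interaction: 39%, 41%, 45%.
- With no effect, these pairs differ in about 6% to 9% of trials.
- With 86 per arm (t-test power about 0.90), t-test against interaction falls to 21%, 14% and 10%.

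Reading the ANOVA on its group term instead gives 33% to 53% against the adjusted regression. That term averages in the baseline visit, where no effect exists, which dilutes 0.5 SD to (0 + 0.5 + 0.5)/3 = 0.33 SD. The sentence on the ANOVA concerns differences at the assessment times, which fits the interaction better, so the interaction figures are the ones carried forward.

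**The case against.** The strongest objection is that ranking primary and supportive analyses is normal content for a statistical analysis plan. That plan and the full protocol are not shown, and listing several analyses is neither wrong nor contradictory in itself. The section also promises effect sizes for non-significant results, which works against selective reporting. This limits how serious the point is but does not remove it. The article does not leave the choice open. It commits to an ANOVA and a regression, both aimed at the group effect, under one common level. Followed as written, that exceeds 5% per score.

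A second objection is that the opening lines on t-test, Mann-Whitney and Chi-square read as a general toolkit and may be meant for baseline comparisons. That is possible, and the text does not settle it. Dropping the two-sample test altogether still leaves about 8% for the interaction and the adjusted regression, so the core does not rest on it.

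A reader might also infer three stronger things, none of which the article supports.
- *That the three analyses all answer the same question, at one visit.* They target different contrasts, the ANOVA uses all visits, and the role of the two-sample test is not stated.
- *That the error rate is about 12%.* A figure that high needs both ANOVA terms to be read, or a t-test, interaction and adjusted regression together at a correlation of about 0.8. The article fixes none of these.
- *That the analyses will often disagree in any event.* That holds when there is a true effect and power is low. Much of it comes from the planned power of 0.5, which is a separate matter.

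**Conclusion.** The point holds as a matter of overlapping, unranked analyses. If any of them may support a claim, the false-positive risk for one score is roughly 7% to 13% against the stated 5%; every combination of the ANOVA with another test exceeds 5%. With a true effect of 0.5 SD at the planned size, the interaction and either of the other tests differ on significance in about 20% to 45% of trials, and in about 6% to 9% with no effect. The ranges rest on the assumptions listed in the working and move with the ANOVA term read, the regression covariates and the correlation between visits. The change is worth making, at moderate priority: it does not invalidate the design, and an unseen analysis plan may already settle the ranking.

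**What to change.** In the Statistical methods section, name one decisive test for the quality-of-life objective: the group coefficient of the planned linear regression, adjusted for the baseline score, for the quality-of-life score at one stated visit, at two-sided 0.05. State that the two-factor ANOVA and the t-test or Mann-Whitney test are supportive, are reported with estimates and intervals, and cannot by themselves support a claim of effect. If an analysis plan exists, it should say the same.

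This brings the false-positive risk for that claim back to 5%. It needs one or two sentences and no extra patients or data, because the regression is already planned and the baseline score is already collected. The small downside is that a significant supportive analysis can no longer be claimed as the result.

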## Abstract

Different musculoskeletal conditions affect people all over the world and were considered by the WHO to be the main cause of disability in 4 of 6 regions in 2017, with an increase in the associated burden and the impact they have on today's society. One of these conditions is related to the knee, which is associated with complex and vulnerable injuries associated with ligaments, menisci, and cartilage. After surgery, there is a reflex inhibition of motor neurons and immobilization, there is rapid atrophy and weakness in the different associated muscles, affecting proprioception, strength and muscle function, compromising quality of life. The aim of this article is to describe a protocol for a rehabilitation program after surgery for people with knee injuries. An experimental study will be carried out with 75 patients, with control and experimental groups. In both groups, initial measurements will be compared with measurements after the program, at different times. It is hoped that this study will generate significant information on rehabilitation intervention for people with knee injuries.

Specifications table

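### No between-group analysis names the T0 score as a covariate, although T0 is collected for every PROM; stating T0 adjustment would gain precision at no cost in data

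*Protocol article*

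**What the plan says.** Under Procedures and Evaluation, the protocol article has all three PROMs measured at baseline (T0), just after the intervention (T1) and six months after it (T2). The Abstract also describes a before-after comparison: "In both groups, initial measurements will be compared with measurements after the program, at different times".

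Statistical methods then names the inferential analyses:

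- a Student's t-test for independent groups, or a non-parametric fallback: "Non-parametric tests, Chi-square and Mann-Whitney U will be used when the normality of the distribution is not verified";
- a two-factor ANOVA for group differences across the assessment times;
- a regression: "A Multiple Linear Regression will be carried out with each dependent variable and the intervention".

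No T0 covariate, change score or analysis of covariance is named.

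Sample size calculation gives the planning figures: "determining a minimum of 60 patients assuming an alpha error of 0.05", power 0.5 and "an effect size of 0,5". Allowing for 20% loss, "a total of 75 patients will be recruited".

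**The concern.** The patient's own score before the intervention is often a strong predictor of the later score. Putting it in the model as a covariate removes the outcome variance that it explains, and corrects the estimate for any T0 difference between the groups. A t-test on the follow-up score does neither.

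A T0 difference is not a remote possibility at this size. With 30 per group, the standard error of a T0 difference in means is sqrt(2/30) = 0.26 SD, about half the planned effect of 0.5 SD. A trial planned at power 0.5 has no precision to spare, and the T0 data are collected anyway.

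The two-factor ANOVA does not settle the matter. The article does not say whether time is a within-patient factor, or whether the group effect or the group-by-time term answers the study question.

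**Working it through.** **Inputs from the article.** Alpha 0.05, power 0.5, effect size 0.5, 60 evaluable patients, 75 recruited, 20% loss.

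**Assumptions, not in the article.** Two-sided test; 1:1 allocation; effect size read as a standardised mean difference; equal SD (set to 1) at each time; T0-to-follow-up correlation r = 0.3, 0.5 or 0.7.

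**Step 1: reproduce the plan's figure.**
- Normal approximation, n per group = 2(z_0.975 + z_0.5)²/d² = 2(1.96 + 0)²/0.25 = 30.7, so 31 per group and N = 62. This is within two patients of the stated 60.
- The exact t-test needs 32 per group, N = 64. A one-sided test gives N = 44 (normal) or 46 (t) and does not match.
- Recruitment: 60/(1 - 0.20) = 75, an exact match.

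**Step 2: power with 30 per group at one follow-up time.** The noncentrality parameter is 0.5 × sqrt(60/4)/sqrt(V) = 1.936/sqrt(V), where V is the variance relative to that of the follow-up score. Power is from the noncentral t distribution.

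| Analysis | V | r = 0.3 | r = 0.5 | r = 0.7 |
|---|---|---|---|---|
| Follow-up score alone | 1 | 0.478 | 0.478 | 0.478 |
| Change from T0 | 2(1 - r) | 0.363 | 0.478 | 0.691 |
| T0 as covariate | 1 - r² | 0.514 | 0.594 | 0.760 |

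With T0 as covariate the residual variance falls by r², that is by 9%, 25% and 49%. The normal approximation for the follow-up score alone gives 0.491.

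**Step 3: the two readings of the two-factor ANOVA.**
- *Group-by-time term, read as change from T0 at one follow-up time.* This is the second row. It is below the covariate model at every r, because 2(1 - r) - (1 - r²) = (1 - r)², which is positive for r < 1. For r < 0.5 it is also below using the follow-up score alone.
- *Group main effect over T0, T1 and T2.* Assume equal correlations and the same effect of 0.5 at T1 and T2. The averaged effect is (0 + 0.5 + 0.5)/3 = 0.333 and the variance of a patient's mean is (1 + 2r)/3. The noncentrality parameter is 0.333 × sqrt(15)/sqrt((1 + 2r)/3) = 1.768, 1.581 and 1.443, and power is 0.412, 0.343 and 0.295. Averaging in T0, where the programme can have had no effect, dilutes the difference.

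**Step 4: sensitivity to loss.** If all 75 were evaluable, power would be 0.570 for the follow-up score alone and 0.610, 0.694 and 0.849 with T0 as covariate. The ordering is the same.

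**The case against.** The best defence has four parts.

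1. **T0 is used.** A reader might infer that the plan ignores T0 altogether. The text does not support that. T0 is one of the ANOVA's assessment times, and if time is a within-patient factor the group-by-time term compares change from T0. Against that comparator the gain at r = 0.7 is about 7 points (0.691 to 0.760), not 28. This stands and limits the claim: T0 is never named as a covariate, and its use as a time level is the less efficient one.
2. **The regression is called multiple.** That word implies predictors beyond the intervention, and a condensed article may leave the list to the full protocol or analysis plan. So T0 adjustment is unspecified rather than excluded. This also stands. It does not remove the point, because the only predictor named is the intervention and the t-test has no place for T0.
3. **The size rests on r.** The correlation is assumed. At r = 0.3 the gain over the follow-up score alone is under 4 points. That is so, and it is why a range is shown.
4. **Allocation is not described.** The text shown does not describe randomisation. If allocation is not random, covariate adjustment and change scores can estimate different quantities. The precision argument is cleanest for groups that differ at T0 only by chance.

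Other strong readings fail. A reader might infer that the trial has under 50% power, but the article states 0.5; the 48% is a recalculation for exactly 60 evaluable patients, and it is 57% with all 75. A reader might fear that choosing the test by normality inflates false positives. The article names no normality test and tolerates small deviations, and simulations with assumed skewed scores gave type I error of only about 5-6%. The Abstract's before-after comparison might suggest that recovery within a group will be credited to the programme, but Statistical methods plans differences between groups. Chi-square beside Mann-Whitney U is loose wording, yet it suits the categorical EQ-5D-5L dimensions.

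**Conclusion.** The point holds as one of precision and specification. The named t-test or Mann-Whitney U and the regression give only group, and the ANOVA uses T0 only as another assessment time. With 60 evaluable patients, power at one follow-up time is about 48% for the follow-up score alone, 36-69% for change from T0 and 51-76% with T0 as covariate. These figures assume 1:1 allocation, a two-sided 0.05 test, a standardised difference of 0.5, equal SDs and r between 0.3 and 0.7. The covariate model is the best of the three at each r shown; how much it gains depends on an r that the article does not give. The planned analyses are not invalid on this account.

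**What to change.** In Statistical methods, make the main between-group analysis of each PROM score at T1 and T2 a pre-specified linear model, or a mixed model covering both times, of follow-up score on group, T0 score and clinic. Report the adjusted mean difference with its 95% CI at each time, with robust or bootstrap standard errors if residuals are skewed. This replaces the t-test and the regression on the intervention alone.

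State that conclusions rest on this model ahead of the two-factor ANOVA. If the ANOVA is kept, say whether time is a within-patient factor and which term is read. Keep Mann-Whitney U as a sensitivity analysis and chi-square for categorical items.

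The cost is a few sentences of analysis text. No extra patients, visits or data are needed, because T0 scores and clinic are already known.
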